## Materials and methods

### General design

SHIP-AGE/MV-FIT is a prospective, longitudinal, population-based observational study, designed in accordance with STROBE guidelines. Recruitment period of the study from 2024-04-03 to 2025-09-30.

### Research ethics approval

This study was approved by the University Medicine Greifswald Ethics Review Board on 30th of June 2023 with identification number: BB 161/22. The research protocol has been preregistered at clinicaltrials.gov under the record identifier NCT05962203.

### Study setting

Adults aged 65 years or older in Mecklenburg-West Pomerania (MV) will be included. All sexes are eligible for participation. Baseline and follow-up examinations will take place at the University Study Center at the Hospital Wolgast. The recruitment is monitored very closely so that, if necessary, adaptations can be made in order to avoid large delays. These objectives may be realized through the inclusion of additional study sites, such as the University Medical Center in Rostock—the other university in MV with which we maintain strong collaborations.

### Eligibility criteria

Inclusion/exclusion criteria were made as simple as possible to recruit a largely heterogeneous (“real world”) elderly population.

Inclusion Criteria: Age 65 years or older, mGFR >30 mL/min per $1.73\;{\text{m}}^{2}$, being able to understand and give written informed consent.Exclusion Criteria: Bedridden, palliative, inability to consent, severe dementia, inability to speak, lack of compliance (paracusis, inability to fulfill at least 60% of the assessments).

Recruitment is promoted through various regional media and communication channels. These include advertisements in local newspapers, publications in municipal bulletins, flyers, and information on websites and digital platforms. Additionally, local networks and community structures are utilized to reach interested older adults and encourage broad participation. We will establish networks with ambulatory practices and stakeholders to recruit and follow the patients. In terms of CKD patients, we will contact local nephrologists in practice. All sites are located in MV.

Participants will be stratified by mGFR: into (a) individuals with mGFR, 30-60 mL/min per 1.73 m2 or urine albumin/creatinine ratio (UAC) ≥300 mg/g and (b) individuals with mGFR, >60 mL/min per $1.73\;{\text{m}}^{2}$ and urine albumin/creatinine ratio (UAC) <300 mg/g. Approximately 328 participants (40%) are expected to have mGFR, 30-60 mL/min per $1.73\;{\text{m}}^{2}$ and 492 participants (60%) are expected to have mGFR, >60 ml/min/$1.73\;{\text{m}}^{2}$ (Fig 2). The planned minimum follow-up duration for participants is three years, while the maximum follow-up duration is approximately six years.

### Subjects information and consent

Interested individuals will receive written information a few days before their enrollment visit and will be informed in person upon arrival at the study center. Both written and oral consent will be required for participation.

### Study timeline

Study start: 2023-09-01; Study completion (estimated): 2030-09-30

### Study outcomes

The primary outcome will be frailty at 36 months post subject inclusion (i.e. Frail vs. non-Frail). Secondary endpoints are: Frailty score transition (pre-frailty), mGFR transition, patient welfare, ability to live independently, quality-of-life scales, burden of CKD on health status, cognitive decline, number of falls, admission to hospitals, referrals to nursing homes, all-cause mortality in primary care. Secondary endpoints will be determined using a broad spectrum of standard geriatric and research assessments as shown in Table 1 (for Abbreviations: see Table 2). Identification of novel parameters may be helpful for early detection of patients at risk for falls.

### Sample size

We performed a sample size calculation for the SHIP-AGE/MV-FIT cohort. A 3-year prevalence of frailty of 20% is expected in individuals with mGFR 30-60 mL/min per $1.73\;{\text{m}}^{2}$ and a prevalence of 12.5% in individuals with mGFR >60 ml/min/1.73 m2. The effect size of the GFR group on frailty is expressed by the odds ratio (OR) between mGFR-group 30-60 mL/min per $1.73\;{\text{m}}^{2}$ compared to the reference group mGFR >60 mL/min per $1.73\;{\text{m}}^{2}$. In multivariable adjusted models with frailty as independent variable, OR per 10 mL/min/$1.73\;{\text{m}}^{2}$ decrease of mGFR was reported to be 1.2 (Cardiovascular Heart Study) [14] and 1.4 (Modification of Diet in Renal Disease study) [18]. An OR of 1.83 was reported in multivariable logistic regression analysis when comparing mGFR 30-44 to ≥45 mL/min per $1.73\;{\text{m}}^{2}$. The target sample size was computed with G*Power by expecting a multivariable adjusted effect size of OR=1.75 in logistic regression analysis with 3-year frailty as the binary response variable. Statistical power was set to 80%, type I error rate was set to 5% and group imbalance is expected (40% will have mGFR, 30-60 mL/min per $1.73\;{\text{m}}^{2}$). Under these conditions one-sided testing led to the required sample size of 616 individuals to be analysed. To further adjust for drop-outs (lost-to-follow-up, deaths, no longer willing or capable to participate in the study), the sample size was corrected for a 25% drop-out rate justifying that 820 volunteers will be enrolled at baseline. The overall goal for recruitment is 820 participants, although the final enrolment number may be between 700 and 1,000.

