A 2016 review (DEGS1, ESTHE, KORA-Age, LUCAS cohorts) showed that the prevalence of physical frailty and pre-frailty in Germany (according to Fried phenotype [6]) were 3.1% and 38.3% in women and 2.5% and 35.9 % in men, respectively [7]. Falls occur at least once annually in 29% of community-dwelling adults 65 years or older — a rate of 0.7 falls per person-year [2]. With the demographic change in Germany, the proportion of the elderly in the population with fall injuries continues to rise. According to the 2016 report from the Federal Statistical Office, almost 6.8 million older people (65+) underwent surgery in Germany in 2014, with fall injuries being the third or second leading cause in men and women, respectively [8]. Multi-component intervention strategies (multi-component healthcare) are part of guideline-based care for reducing frailty and the risk of serious fall injuries of elderly persons [2]. However, the implementation of these intervention strategies in primary care is poor. We will introduce this intervention in primary care to reduce frailty in individuals aged 65 years or older in MV. Consequences should be less hospital admissions, less medication, better quality of life, longer life in their “own walls” and avoid acute illnesses. We will establish networks between hospital-based patient care and general practitioners (GPs), public, and private healthcare providers to bridge gaps between inpatient and outpatient primary care of old patients in rural MV. We expect that treatment and care across the in-hospital and primary care sector for elderly (Intersectoral Care Manangement, ICM) will stimulate new pathways of discharge management at the university hospital. Our strategy offers health care to the elderly keeping them as long as possible as active, non-frail and off-dialysis individuals that they can contribute to the society rather than being a “burden”.

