### 3. Evidence and objectives

The oldest definition of frailty, and one of the most widely used, is the phenotype developed by Fried *et al*. [6]. Frailty is defined as a clinical syndrome in which 3 or more of the following criteria are present: (1) weight loss, (2) slowness, (3) exhaustion, (4) weakness, and (5) low physical activity [6, 13] . Three large-scale studies addressed a possible role of reduced kidney function on frailty in the elderly. In all three studies, frail individuals were identified using the definition developed by Fried et al[6]. CKD stages were defined by KDIGO criteria (https://kdigo.org). 1) Dalrymple *et al*. investigated whether lower levels of kidney function were associated with prevalent or incident frailty in Cardiovascular Health Study (CHS, n=4,150; age ≥ 65 years) participants without stroke, Parkinson disease, prescribed medications for Alzheimer disease or depression, or severely impaired cognition [14]. The primary predictor was eGFR calculated using serum cystatin C (eGFRcys). Secondary analyses examined eGFR using serum creatinine (eGFRSCr). Outcomes were prevalent frailty and incident frailty at 4 years of follow-up. The authors found that lower eGFRcys was associated with a higher risk of prevalent and incident frailty whereas lower eGFRSCr was not. Nearly one fourth of older adults with an eGFRcys <45 ml/min per $1.73\;{\text{m}}^{2}$ (KDIGO <Stage 3a) had prevalent frailty. The findings were attenuated when the authors used the 2012 CKD-EPI cystatin C equation adjusted for demographic characteristics. However, the 2012 CKD-EPI cystatin C equation was not derived in an elderly cohort, and the age coefficient may not be optimal in the elderly. Thus, the authors were unable to demonstrate evidence for a role of reduced kidney function on prevalent or incident frailty. Similar results were observed in the Outcomes of Sleep Disorders of Older Men (MrOS Sleep) study cohort [15]. Together, the data highlight the importance of considering non-GFR determinants of kidney function, e.g. accelerated loss of lean muscle mass, which is thought to be an underlying process in frailty. 2) Ballew *et al*. investigated the cross-sectional association of frailty with kidney function. Kidney function was measured by several biomarkers (creatinine, cystatin C, and urine albumin) in The Atherosclerosis Risk in Communities (ARIC) Study cohort, which is biracial population-based cohort of men and women 66 years or older in the United States [13]. Among the 4,987 participants (men and women aged 66 years and older), 341 were classified as frail. Reduced eGFR (<60 mL/min/$1.73\;{\text{m}}^{2}$) was common in frail individuals, but the proportion with eGFRs <60 mL/min/$1.73\;{\text{m}}^{2}$ was much greater when kidney function was estimated using eGFRcys compared to eGFRScr (77% vs 45%). The authors concluded that cystatin C-based eGFRcys may be a much better marker of kidney function in frail individuals, with lower levels of eGFRcys independently associated with frailty. However, cystatin C level may be high in the setting of inflammation, which means that associations between frailty and eGFR based on cystatin C level may be driven by chronic inflammation rather than CKD itself. Often CKD is characterized by an inflammatory state, and higher inflammatory burden has been associated with frailty. 3) Guerville *et al*. investigated whether a fast decline on eGFR would be associated with incident frailty in community dwellers, aged ≥70 (n=833) in the Multidomain Alzheimer Preventive Trial (MAPT) [16]. The authors calculated eGFR using serum creatinine, age, sex in the eGFR CKD–EPI equation. Frailty occurred in 95 (11%) participants between 24 and 60 months. The authors concluded that people with fast eGFR decline are at risk for frailty incidence. However, since the difference between eGFR was determined at relatively short follow up intervals (24 months), this approach may have misclassified people with creatinine fluctuations instead of people with fast eGFR decline. Therefore, variations of serum creatinine may have accounted for variations of kidney function or muscle mass (possibly influenced by the multi-domain intervention), but were not addressed in this study [16].

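### The 616 analysed give 80% power only for an unadjusted two-group comparison, yet the figure is presented as power for the multivariable-adjusted odds ratio

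*Protocol article*

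**What the plan says.** The calculation is in the protocol article, Materials and methods, Sample size.

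- Assumed rates: "A 3-year prevalence of frailty of 20% is expected in individuals with mGFR 30-60 mL/min per" 1.73 m², against "a prevalence of 12.5% in individuals with mGFR >60 ml/min/1.73 m2".
- Effect: "The target sample size was computed with G*Power by expecting a multivariable adjusted effect size of OR=1.75 in logistic regression analysis".
- Error rates: "Statistical power was set to 80%, type I error rate was set to 5% and group imbalance is expected", with 40% in the lower mGFR group.
- Result: "Under these conditions one-sided testing led to the required sample size of 616 individuals to be analysed".
- Enrolment: 820 after a 25% drop-out correction, "although the final enrolment number may be between 700 and 1,000".

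Table 1 names multivariable logistic regression as the primary statistical method. Statistical methods lists what enters the model beside baseline mGFR: pre-existing frailty, a frailty index, sex, BMI, age, comorbidities, medication, depression score and quality of life. The Introduction (1. Relevance) says that kidney function declines with age. The article states no R² between mGFR group and the other covariates, and Statistical methods does not repeat that the primary test is one-sided.

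**The concern.** The paragraph attaches 80% power to an adjusted effect in a multivariable model. Two of its own features point to an unadjusted calculation: the odds ratio equals the crude contrast of the two assumed rates, and the sample size matches a formula with one predictor and nothing else. When the exposure is correlated with the covariates, the variance of its adjusted coefficient rises by about 1/(1 − R²), where R² is the share of variation in mGFR group explained by the other covariates. Power at a fixed adjusted odds ratio falls accordingly.

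The calculation serves the primary outcome and the study's central hypothesis. If the result is null, readers will judge it against a stated 80% that the planned model does not have. The enrolment range raises a related point: its lower end falls short of the article's own required number.

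**Working it through.** **Inputs.** From Sample size: p0 = 0.125, p1 = 0.20, share in the lower mGFR group B = 0.40, one-sided α = 0.05, power 0.80, drop-out 25%, enrolment 700 to 1,000. Assumed, because the article gives no value: R² = 0.05 to 0.30.

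**1. The odds ratio.** (0.20/0.80)/(0.125/0.875) = 0.25/0.142857 = 1.75. The crude and the adjusted odds ratio are the same number.

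**2. Reproducing 616 with R² = 0.**

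- Variance term: V = 1/(0.6 × 0.125 × 0.875) + 1/(0.4 × 0.20 × 0.80) = 15.238 + 15.625 = 30.863.
- Wald formula: N = (1.645 + 0.842)² × V/(ln 1.75)² = 6.183 × 30.863/0.3132, about 610.
- Hsieh formula, equivalent here to comparing two proportions: 614.
- Wald with a variance correction: 619 to 622, depending on how the correction is approximated.

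These bracket 616. Alternatives do not: R² = 0.05 needs 646 to 652, a continuity correction gives about 668, and a two-sided 5% test needs 774 to 790.

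**3. Drop-out.** 616/0.75 = 821.3, so 820 is consistent; 820 × 0.75 = 615.

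**4. Power with covariates, adjusted odds ratio held at 1.75.** With the variance correction,

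power = Φ{[ln(1.75) × √(N(1 − R²)) − 1.645 × √(0.75·V0 + 0.25·V)]/√V},

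where V0 = 1/(0.4 × 0.6 × 0.155 × 0.845) = 31.813 and 0.155 = 0.6 × 0.125 + 0.4 × 0.20.

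Example, N = 616 and R² = 0.2: √492.8 = 22.20; 0.5596 × 22.20 = 12.42; 1.645 × √31.575 = 9.24; (12.42 − 9.24)/5.556 = 0.572; Φ = 0.72.

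| R² (assumed) | One-sided power at 616 | Analysed needed for 80%, 616/(1 − R²) | Enrolled, /0.75 |
|---|---|---|---|
| 0 | 80% | 616 | 822 |
| 0.05 | 78% | 649 | 866 |
| 0.10 | 76% | 685 | 914 |
| 0.20 | 72% | 770 | 1,027 |
| 0.30 | 67% | 880 | 1,174 |

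At 615 analysed, the odds ratio detectable with 80% one-sided power is about 1.80 for R² = 0.1, 1.86 for 0.2 and 1.93 for 0.3.

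**5. The enrolment range.**

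- 700 × 0.75 = 525 analysed: one-sided power about 74% with R² = 0 and 66% with R² = 0.2.
- 1,000 × 0.75 = 750 analysed: about 86% with R² = 0 and 79% with R² = 0.2.

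The top of the range therefore covers R² up to about 1 − 616/750 = 0.18.

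**6. Two-sided 5%, for reference.** At 616 analysed: about 70% with R² = 0, 65% with 0.1 and 60% with 0.2.

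**The case against.** **The arithmetic is right.** Both 616 and 820 follow from the stated inputs. This stands: the fault is the claim attached to the number, not the calculation.

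**The size of the loss is assumed.** This also stands. At R² = 0.05 it is about 2 points; at 0.3 it is about 13. What the article does settle is that R² is not zero, because age is in the model and kidney function is said to decline with it.

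**The equal odds ratios may be a labelling matter.** The section cites multivariable odds ratios from other studies as the basis for 1.75, and 20% may simply be what 12.5% and 1.75 imply. That is possible, and it is why the article should say which is meant. It does not rescue the power: if 1.75 is the adjusted value, the covariate allowance is missing. A conditional odds ratio can exceed the marginal one when covariates are strongly prognostic, and continuous mGFR or Cox regression could recover some power. The calculation, however, is for a two-group logistic contrast with the adjusted odds ratio fixed at 1.75.

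**The low end of enrolment is not the likely case.** The goal is 820. With 505 enrolled from 3 April 2024 to 5 March 2025 (336 days), the same pace to 30 September 2025 (545 days) gives about 505 × 545/336 = 819. This stands as a forecast, but the article offers 700 as acceptable, and 525 is below its own requirement.

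**Two stronger readings are not supported.** A reader might infer that true power is nearer 55 to 70%. That depends mainly on switching to a two-sided test. One-sided testing is openly stated, the hypothesis is directional, and Statistical methods does not state a two-sided test. A reader might also infer that the implied overall frailty of 15.5% is contradicted by figures quoted in the Introduction: German rates that "were 3.1% and 38.3% in women and 2.5% and 35.9 % in men, respectively" for frailty and pre-frailty; "Among the 4,987 participants (men and women aged 66 years and older), 341 were classified as frail", or 6.8%; and 11% incident between 24 and 60 months. The first two are cross-sectional and the third is incidence in another cohort, whereas the assumption is prevalence at three years in a sample expected to be 40% mGFR 30-60. The same Introduction reports about a quarter frail among those with cystatin-based eGFR below 45. These figures do not show 15.5% to be wrong.

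**Conclusion.** The point holds in this form. The figure of 616 gives 80% power for a one-sided 5% comparison of two mGFR groups without covariates, but it is presented as power for a multivariable-adjusted odds ratio of 1.75. Under the article's own premise of an adjusted 1.75, any R² above zero takes power at 616 below 80%: to between 78% and 67% one-sided over the assumed range. Only that range can be given, because the article supplies no R². Independently of R², the lower enrolment bound misses the stated requirement by 616 − 525 = 91 analysed participants. The one-sided test is a disclosed choice that the analysis section should repeat, not a hidden error.

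**What to change.** Rewrite the Sample size paragraph to:

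- state the R² with other covariates that was entered in G*Power;
- say whether 1.75 is the crude or the adjusted odds ratio, and give the other if it differs;
- give power, or the odds ratio detectable with 80% power, for R² of 0.05 to 0.3 and for 525 to 750 analysed.

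In Statistical methods, state that the primary test is one-sided at 5%, as the sample size assumes, and give the reason. Report the two-sided power alongside (about 70% at 616 with R² = 0) for readers of two-sided confidence intervals. Checking the 15.5% assumption against pooled frailty in those already enrolled is optional.

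The cost is one paragraph and one sentence, and a less favourable stated power. No participants are added, and data collection and the analysis model do not change.

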### Data management

Data and documents are documented on the eHealth platform of the University Medicine Greifswald. Data reports are regularly extracted from the eHealth platform to check completeness and plausibility of the data (quality assurance). Data collections will be accompanied by a continuous data monitoring with standardized reporting.

### Status of study

As of March 5, 2025, more than 2,000 eligible individuals have been registered, with 505 participants enrolled in the study.

### Statistical methods

Evaluation of the impact of CKD on frailty among elderly persons The primary outcome Frail vs. non-Frail and events observed in the follow-up period will be analyzed using multivariable logistic regression. Furthermore, in case of proportional hazards, multivariable Cox regression analysis will be conducted to study the time to frail, which usually has a higher statistical power than logistic regression. Main exposure variables that enter both models are mGFR at baseline, pre-existing frails, frailty-index, sex, BMI, age, comorbidities/medical history, medication, geriatric depression score, and quality of life (see assessments). In univariable analysis all possible predictor variable will be checked in relation to the response variable whether a transformation of axis (e.g. log-transformation), spline-usage, or (re-)categorization seems appropriate and medically plausible for the use in multivariable models. In case of mGFR, we include baseline measurements, gender-specific quantile probabilities, and absolute and relative mGFR changes if available. Interaction terms will be used in model equations based on prior knowledge (evident interactions) and other (currently unknown) interaction effects will be tested for a significant increase in the model performance. Event variables (obligation to dialysis, hospital re-admission, referrals to nursing homes, all-cause mortality, etc) will be analyzed with penalized multivariable logistic regression. In order to create complete cases, we make use of imputed datasets (e.g. by Multiple imputation using Fully Conditional Specification or by Random Forest imputation). The model size will be controlled by setting regularization parameters (Elastic net or LASSO) and repeated internal cross-validation will be used to avoid overfitting and to generate more robust estimates that can result in a very generalizable model. Secondary endpoints such as the patient-individual changes in mGFR and in the frailty score will be analyzed in linear mixed effects models. Implementation of multi-component healthcare will be monitored by usage of the regional digital health records. If necessary, the results of formative process analysis are used to adapt processes or the documentation.

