
### 4. Measurements

In the SHIP-AGE/MV-FIT study we will observe 820 participants over a period of 3 years. Informed consent will be obtained for participation in the study. Subjects who consent will be screened for eligibility and if the inclusion and none of the exclusion criteria are fulfilled, subjects will be enrolled. Data obtained from the screening, and enrollment visits must be supported in the patient’s source documentation, i.e. in the geriatric health record (eCRFs). Our follow-up (visits at 1st year and every 12 months) is designed to collect these data and to strengthen compliance to the individual interventions.

Screening Visits/Baseline: Adults aged 65 years or older will be enrolled if eligible. If eGFR (CKD-EPI) is known and >25 mL/min per $1.73\;{\text{m}}^{2}$, mGFR will be measured. Scheduled examination components and timeline by visits are shown in Fig 1.

Geriatric assessments and evaluations: Tables 1 and 2 show the assessments and evaluations. The GAITRite walkway system is the current gold standard in gait analysis. Leonardo mechanography, TUG, 5CRT are other physical measures.

**Table 1 pone.0324001.t001:** Frailty, renal function, and the effect of multi-component intervention strategies.

Design:	Prospective, longitudinal, observational study
All patient intervention:	Aerobic and resistance exercise and others (multi-factorial geriatric assessment monitoring and management systems)
Inclusion criteria:	Out-patients, aged ≥65 years, mGFR ≥30 mL/min per $1.73\;{\text{m}}^{2}$
Exclusion criteria:	Bedridden, palliative, inability to consent, severe dementia (MMSE<12), inability to speak, inability to fulfill at least 60% of the assessments
Primary outcome:	Frail vs. non-Frail
Secondary:	Frailty score transition (pre-frailty), mGFR transition, patient welfare, ability to live independently (off-dialysis), quality-of-life scales, burden of CKD on health status, cognitive decline, number of falls, admission to hospitals, referrals to nursing homes, all-cause mortality in primary care
Primary statistical method:	Multivariable logistic regression
Further statistical analysis:	Multivariable Cox regression, Chi-Square-Test, Propensity score matching

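### The number of falls is a count endpoint, but the only model the plan gives for follow-up events is logistic regression; an any/none analysis would discard more than half of the information on falls

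*Protocol article*

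**What the plan says.** Study outcomes in the protocol article includes among the secondary endpoints "cognitive decline, number of falls, admission to hospitals, referrals to nursing homes, all-cause mortality in primary care". Table 1 repeats this list, and Table 2 collects falls as a number under medical history.

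Statistical methods assigns models as follows:

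- Primary outcome and follow-up events: "The primary outcome Frail vs. non-Frail and events observed in the follow-up period will be analyzed using multivariable logistic regression".
- An open list of event variables: "Event variables (obligation to dialysis, hospital re-admission, referrals to nursing homes, all-cause mortality, etc) will be analyzed with penalized multivariable logistic regression".
- Some quantitative secondary endpoints: "Secondary endpoints such as the patient-individual changes in mGFR and in the frailty score will be analyzed in linear mixed effects models".
- Cox regression is described only for time to becoming frail.

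Under further analyses, Table 1 gives only "Multivariable Cox regression, Chi-Square-Test, Propensity score matching". No Poisson, negative binomial or recurrent-event model is named.

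The Relevance section supplies two background figures on falls: "Falls occur at least once annually in 29% of community-dwelling adults 65 years or older" and "a rate of 0.7 falls per person-year".

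**The concern.** A binary model cannot estimate a number of falls. Once falls are reduced to any or none, a participant with one fall in three years and a participant with ten are the same case. Falls cluster in repeat fallers, so much of the information on a difference between the kidney-function groups lies in the part that is dropped. The contrast also shrinks over a long window, because many participants in both groups will have fallen at least once. Both effects occur even if everyone is followed for the same time.

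Fall prevention is a stated purpose of the programme. At stake is whether the study can describe an excess of falls in CKD, if there is one, on the endpoint it lists.

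**Working it through.** **The plan's own sample size.** The article states no power for falls, so the check starts from the primary outcome. It assumes "A 3-year prevalence of frailty of 20% is expected in individuals with mGFR 30-60 mL/min", 12.5% in the reference group (OR 1.75), a 40/60 split, 80% power and a one-sided 5% test. A two-proportion calculation with these inputs gives about 613 in total, against the stated 616. Dividing 616 by 0.75 gives 821, against 820 enrolled. The planning size is therefore sound, and 616 is used below (369.6 with mGFR above 60, 246.4 with mGFR 30-60).

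**Clustering of falls.** If falls were Poisson at 0.7 per year, the share falling at least once would be 1 − exp(−0.7) = 50%, not 29%. For a negative binomial with mean μ and dispersion k, P(no fall) = (1 + kμ)^(−1/k). Solving (1 + 0.7k)^(−1/k) = 0.71 gives k = 3.77.

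**Formulas** (unadjusted Wald tests, two-sided 5%; 0 = reference group, 1 = mGFR 30-60, μ1 = RR × μ0):

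- Count model: Var(log RR) = (1/μ0 + k)/n0 + (1/μ1 + k)/n1.
- Any/none: a = 1 − (1 + kμ)^(−1/k) in each group; Var(log OR) = 1/[n0·a0(1 − a0)] + 1/[n1·a1(1 − a1)].
- z = estimate / √variance; power = Φ(z − 1.96); relative efficiency = (z for any/none ÷ z for count)².

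**Three years, μ0 = 2.1, individual tendency constant, assumed RR 1.5:**

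- Count: variance = 4.250/369.6 + 4.091/246.4 = 0.0281; z = 0.4055/0.1676 = 2.42; power 68%.
- Any/none: 44.0% against 49.2%, OR 1.23; variance 0.0272; z = 0.2089/0.1650 = 1.27; power 24%.

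**One year, μ0 = 0.7, assumed RR 1.5:**

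- Count: variance = 5.202/369.6 + 4.726/246.4 = 0.0333; z = 2.22; power 60%.
- Any/none: 29.0% against 34.6%, OR 1.30; variance 0.0311; z = 0.2583/0.1763 = 1.47; power 31%.

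Simulation with the dispersion estimated (600 runs per setting) gave 67% against 26% over three years and 62% against 31% over one year.

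**Over a range of assumed rate ratios (two-sided power, count model / any-none):**

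| RR | 1 year | Relative efficiency | 3 years | Relative efficiency |
|---|---|---|---|---|
| 1.2 | 17% / 10% | 0.45 | 19% / 8% | 0.29 |
| 1.3 | 30% / 16% | 0.45 | 34% / 13% | 0.28 |
| 1.5 | 60% / 31% | 0.43 | 68% / 24% | 0.27 |
| 1.75 | 87% / 52% | 0.42 | 92% / 41% | 0.26 |
| 2.0 | 97% / 69% | 0.41 | 99% / 56% | 0.26 |

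One minus the relative efficiency is the information lost: 55-59% over one year and 71-74% over three. Any/none would need about 2.2-2.4 times the sample over one year, and about 3.5-3.9 times over three, to match the count model.

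**Sensitivity to the baseline rate.** If 0.7 per year is the average of the whole cohort and not of the reference group, then at RR 1.5 μ0 is divided by 0.6 + 0.4 × 1.5 = 1.2. Power becomes 67% against 26% over three years and 58% against 32% over one year.

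**The case against.** **Falls are not expressly assigned to logistic regression.** A reader might infer that the plan prescribes any/none for falls. It does not say so. Falls are reached only through the general word for events and the open end of the event-variable list. The mixed-model sentence is also open-ended and could be read to cover a quantitative endpoint. This stands, and the point is worded accordingly. It does not rescue the text: a Gaussian mixed model also fits a skewed, mostly-zero count poorly, so neither reading gives a suitable model.

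**A journal article may leave one secondary endpoint's model to the analysis plan.** That would answer pure silence. Here the article fixes a model family for follow-up events in general, and that family does not fit one of the endpoints it lists.

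**The loss of power does not follow from the protocol's figures alone.** A reader might infer that more than half the power is lost on those figures. That also needs a rate ratio, a three-year window and a fall tendency that persists across years. Over one year power never halves at 616 analysed. Over three years it halves only for rate ratios of about 1.16-1.86 two-sided, or 1.21-1.63 one-sided. If tendency were independent each year, dispersion over three years would be 3.77/3 = 1.26 and the any-fall shares at RR 1.5 would be 64% (1 − 0.71³) and 72%. Power would then be about 97% against 52%, which is not a halving. This objection stands for power; the loss of information is the supportable statement.

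**Hospital admissions.** A reader might extend the point to them. That endpoint is not worded as a count, and the plan deliberately treats re-admission as an event variable, so a count model would redefine it.

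**The comparison is simplified.** It is unadjusted, whereas the plan uses multivariable and penalized models. The two fall figures are cited background, not planning values for this cohort. Both limits stand.

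**Conclusion.** The point holds as a mismatch between a listed count endpoint and the models stated for follow-up events. The assignment of falls to logistic regression is the most natural reading, not an express one.

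On the article's background figures, any/none discards more than half of the information on falls at every rate ratio tried from 1.2 to 2.0. The one-year range rests on the two published figures and a negative binomial shape. The three-year range also assumes that a person's fall tendency persists. The power figures are illustrations at assumed rate ratios, since the protocol gives none for falls. They do not show that a real association would be missed.

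Falls are one secondary endpoint among several. The primary outcome, its model and the 616/820 sample size are untouched.

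**What to change.** Add one sentence to Statistical methods: the number of falls is analysed by negative binomial regression with log person-time as offset and the planned baseline covariates, reporting rate ratios, with a robust standard error or a sensitivity analysis that caps high counts. Keep any-fall logistic regression as a supplementary analysis. Leave hospital admission and the other event variables as planned.

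The cost is small, because the counts are already collected. The downside is that a rate ratio is more sensitive to a few very frequent fallers, which is why the robust standard error or capped-count analysis should go with it.
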